#### Trial duration

The study has commenced in October 2023 and the recruitment will continue until November 2024. A preliminary analysis will be conducted after 20 participants have completed the program to assess for futlity. If no improvements in participant well-being are found, or wellbeing deteriorates or adverse events are reported the trial will be discontinued. This decision will be made by the research team collaboratively.

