**Methods:**

The trial is a randomized wait-list control trial assessing the effectiveness, feasibility and acceptability of online CRAFT with a parallel group. Participants will be randomised to receive either online CRAFT or to a wait-list control group who are provided with CRAFT related reading material during the waiting period. Outcomes will be assessed at baseline and then at 6- and 15-weeks post baseline. The primary outcome will be improved wellbeing of participating family members. The trial reporting will comply with SPIRIT guidelines.

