## Methods

### Study design

This is a randomized wait-list control trial that will evaluate the effectiveness, feasibility and acceptability of online CRAFT with a parallel group. Participants will be randomised to receive either online CRAFT for 6 sessions over 6 to 10 weeks or to a wait-list control group who are provided with CRAFT related reading materials during the waiting period. Outcomes will be assessed at baseline and then at 6- and 15-weeks post baseline. Outcome measures will be completed online independently of researchers or clinicians. The trial reporting will comply with CONSORT guidelines. Figure 1 provides an overview of the trial recruitment and process.

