### Randomisation and blinding

The randomisation procedure for this project will be conducted by an independent researcher ([name]) using STATA software (Version 18 MP) and with the 'randomizr' package. This researcher will not be involved in other aspects of project implementation, such as CRAFT delivery or data collection. The researcher (NS) who recruits the participants will have no access to the order of allocation. All participants will be allocated an identification number and, before completing their baseline measures, will be randomly allocated to either the CRAFT group or the wait list control group. Individuals randomized to the control group will be assigned a 6-week wait time.

All assessments are conducted online, thus minimizing the possibility of researcher bias. Analysis of results will be blinded to the clinicians delivering CRAFT. The clinicians will be provided with contact information of consenting participants and they will deliver the program as scheduled without knowing which group the person is allocated to. Trial participants will be informed their start date for the intervention as 1. as soon as possible (Group A—within 7 days) or 2. within 6 weeks (Group B—WLC) without being informed which group they are in. The need for unblinding is not anticipated.

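### The futility look is triggered by programme completion, but no wellbeing survey is tied to completion, so a look run at the trigger would use part-treatment data for a substantial share of the 20

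*Protocol article*

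**What the plan says.** All references are to the protocol article.

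- **Trigger** (Trial duration): "A preliminary analysis will be conducted after 20 participants have completed the program to assess for futlity". Neither the arm of the 20 nor the survey to be used is named.
- **Consequence** (Trial duration): "If no improvements in participant well-being are found, or wellbeing deteriorates or adverse events are reported the trial will be discontinued". The research team decides; Ethics and data monitoring provides no data monitoring committee.
- **Programme length** (Study design): "online CRAFT for 6 sessions over 6 to 10 weeks".
- **Start of CRAFT** (Randomisation and blinding): the immediate group starts "as soon as possible (Group A—within 7 days"). For the other arm, "Individuals randomized to the control group will be assigned a 6-week wait time".
- **Surveys** (Abstract, Study design and Table 1): "Outcomes will be assessed at baseline and then at 6- and 15-weeks post baseline". Table 1 also places the record of sessions attended at week 6, although the programme may run to 10 weeks.
- **Late returns** (Recruitment and follow-up procedures): missing follow-up surveys are chased weekly for up to 4 weeks after they fall due.

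**The concern.** The stop rule asks whether people who completed CRAFT improved, yet completion is not a measurement point. Unless the look waits, the most recent survey for many of the 20 will be one taken when some sessions were still to come. For a wait-list completer, the week-6 survey comes before any CRAFT.

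Part-treatment data can be expected to understate the change after the full programme. The error therefore runs towards finding no improvement, and the stated consequence of that finding is discontinuation. A trial of an effective programme could be closed on surveys that could not yet show its effect.

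**Working it through.** The article gives no figure for the timing of the look, so there is none to reproduce. The check is calendar arithmetic, then a simulation.

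**1. When participants finish, in weeks from baseline**

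- CRAFT arm: start 0 to 1, plus 6 to 10 weeks of sessions, gives about 6 to 11. The week-6 survey is 0 to 5 weeks before the end. The week-15 survey is 15 − 11 = 4 to 15 − 6 = 9 weeks after it.
- Wait-list arm: start about 6 to 7, finish about 12 to 17. Week 6 is pre-treatment, and week 15 can come before the end.

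This step needs no assumption about accrual.

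**2. When the 20th completion occurs**

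From the article: 260 participants (Sample size calculation), and "The study has commenced in October 2023 and the recruitment will continue until November 2024", taken as about 56.5 weeks. Assumed: even accrual, 1:1 allocation, 80% completing, session length uniform over 6 to 10 weeks.

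- Accrual: 260/56.5 = 4.6 per week.
- CRAFT-arm participants who will complete: 4.6 × 0.5 × 0.8 = 1.84 per week.
- Time to enrol 20 of them: 20/1.84 = 10.9 weeks.
- Mean time to finish: 0.5 + 8 = 8.5 weeks.
- Trigger: 10.9 + 8.5 = about trial week 19, with about 89 enrolled.

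**3. Share of the first 20 CRAFT-arm completers not yet at week 15**

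With completions as a Poisson stream at rate c per week and mean finishing time m, the share is approximately 1 − 0.95 × [1 − (15 − m) × c/19]. At the planned pace this is 1 − 0.95 × [1 − 6.5 × 1.84/19] = 0.65. Simulation gives:

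| Scenario (CRAFT arm only) | Not at week 15 |
|---|---|
| Planned even pace, 6 to 10 weeks | 65% |
| Planned pace, all take 6 weeks | 81% |
| Planned pace, all take 10 weeks | 47% |
| Linearly rising accrual to 260 | 49% |
| Half the planned pace | 35% |
| A quarter of the planned pace | 20% |

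If wait-list completers count among the 20, the share is about 71% at the planned pace and 37% at half pace.

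**4. Effect on the stop decision (illustrative)**

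Assume that the look stops if mean change in the 20 is zero or worse, that the full gain is d SD of change, that benefit is proportional to sessions received, and that it persists to week 15. Then P(no mean improvement) = Φ(−d × f × √20), where f is the share of the effect visible.

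- Programme delivered by week 6, CRAFT arm: mean of (6 − start)/length, about 71.5% among the first 20 completers in simulation. (For all CRAFT-arm participants it is 5.5 × ln(10/6)/4 = 0.70.)
- Latest available survey: f = 0.35 × 1 + 0.65 × 0.715 = 0.815.

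| Data used | f | d = 0.3 | d = 0.2 |
|---|---|---|---|
| Post-programme | 1 | Φ(−1.34) = 9% | 19% |
| Latest survey | 0.815 | Φ(−1.09) = 14% | 23% |
| Week 6 only | 0.715 | Φ(−0.96) = 17% | 26% |

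**The case against.** The strongest reply is that the article does not say the data are cut at the 20th completion. A look held after 20 people have completed may equally wait until they reach week 15, and an analysis plan that is not shown may settle this. That stands as far as it goes: a reader might infer that the stop decision must rest on part-treatment data, and the text does not support so firm a reading. But the article itself fixes the trigger and attaches a mandatory consequence to it. A trigger that allows either reading is badly fixed, whatever detail is left elsewhere.

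A reader might also infer that most of the 20 will have only a week-6 survey. That holds at the planned even pace, but not at half pace, with 10-week courses throughout, or with linearly rising accrual. Larger wrong-stop figures are possible if wait-list completers' week-6 surveys are scored as completer data with no effect, but nothing in the article says the look would do this. The figures here are therefore for the CRAFT arm only.

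Two further points stand. For someone who finishes in about 6 weeks, the week-6 survey is close to programme end. And because surveys are chased for up to 4 weeks, some week-6 surveys may come back near or after the end; the calculation ignores this and so somewhat overstates the problem.

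Finally, week 6 is the only survey at which the wait-list arm is still untreated, so moving the look to week 15 gives up a clean randomised contrast. The rule as written names no control comparison, but the replacement must not treat wait-list week-15 data as control data.

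**Conclusion.** The concern holds as a mismatch between trigger and survey schedule. The misalignment follows from the article's own dates. Its size depends on pace: if the look is run at the trigger, about 65% of the first 20 CRAFT-arm completers lack a week-15 survey at the planned even pace, and about 20% to 50% do under slower or rising accrual or 10-week courses. All of these assume 80% completion.

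The direction of bias is towards no improvement. The rise from about 9% to 14% or 17% is illustrative only: it rests on an assumed gain of 0.3 SD, benefit proportional to sessions, and a simple mean-change rule that the article does not state. The change is worth making because the rule can end the trial and one amended passage cures the fault. This point is separate from the small number at the look and the absence of a comparator.

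**What to change.** Reconcile Study design, Randomisation and blinding, Table 1 and Trial duration, and tie the look to an outcome survey. In Trial duration:

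- Trigger the look when 20 CRAFT-allocated participants have returned their 15-week survey, or its 4-week chase window has closed. Reaching week 15 is not enough, because a due survey may not have come back.
- Judge post-programme change on all CRAFT-allocated participants whose 15-week survey is due by then.
- Do not let a week-6 survey taken before completion stand in for a post-programme one.
- Do not pool wait-list week-15 surveys as control data. By then those participants have started CRAFT, and with a week-6 start and lengths uniform over 6 to 10 weeks about a quarter (those needing more than 9 weeks) are still mid-programme.

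**Cost.** At even accrual the look moves from about trial week 19 to about 10.9 + 15 = week 26, or slightly later because of the chase window. About 4.6 × 25.9 = 119 people are then enrolled instead of 89. The total sample and the survey schedule do not change. The later look also delays its review of deterioration, but adverse events continue to be reported through the separate pathway to the ethics committee described under Ethics and data monitoring.

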### Objectives of the study

This trial will determine the effectiveness of an online delivered CRAFT counselling intervention for improving the well-being of family members with a loved one experiencing substance problems with and without co-occurring mental health problems. It is hypothesised that CRAFT implemented online by accredited therapists will be more beneficial than CRAFT self-help information provided to the wait-list group. Compared to the wait-list control group, the CRAFT group will show significant decrease in self-reported levels of depression, anxiety and stress and significant increase in life satisfaction and that these improvements will be maintained over a three-month period post intervention.

It is hypothesized that 1) improvements in depression, anxiety and stress scores as a function of CRAFT relative to the control group will be mediated by: a) acceptability of receiving support online and b) ease of access. Given the lack of information regarding implementation parameters of substance use interventions for families of people with a mental health condition, qualitative methods will explore the experiences of study participants as well as clinicians delivering the program. The study has the following specific aims:

Aim 1: determine the effectiveness of an online delivered CRAFT counselling intervention on on self-reported levels of depression, anxiety, stress and life satisfactionAim 2: qualitatively examine the paricipants’ experiences about the acceptability of receiving support onlineAim 3: qualitatively examine the clinicians’ experiences of delivering the program and feasibility

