#### Ethics and data monitoring

Ethical approval has been received from the Charles Sturt University Human Research Ethics Committee (approval number H23769). The establishment of a Data Monitoring Committee is not required for this study because the trial is small scale and of short duration. The population is not particularly vulnerable and the intervention has a known safety profile. Risk management processes are established including reporting pathways for adverse events to the responsible Human Research Ethics Committee.

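### The futility look after 20 programme completers names no comparison with the wait-list arm, so it cannot assess futility, and its adverse-event trigger is unqualified

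*Protocol article*

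**What the plan says.** The Trial duration section sets the look: "A preliminary analysis will be conducted after 20 participants have completed the program to assess for futlity". The consequence follows: "If no improvements in participant well-being are found, or wellbeing deteriorates or adverse events are reported the trial will be discontinued". On who decides, it says: "This decision will be made by the research team collaboratively".

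Other sections bear on this:

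- Objectives of the study states the hypothesis as a contrast between arms: "Compared to the wait-list control group, the CRAFT group will show significant decrease in self-reported levels of depression, anxiety and stress".
- The abstract gives the endpoint: "The primary outcome will be improved wellbeing of participating family members". Table 1 lists four self-report instruments at baseline, 6 and 15 weeks: DASS-21, SWLS, Flourishing Scale and Brief-COPE.
- Randomisation and blinding says of the control arm: "Individuals randomized to the control group will be assigned a 6-week wait time". Wait-list participants then receive the programme too.
- Statistical analysis applies the intention-to-treat principle to all analyses.
- Ethics and data monitoring says "The establishment of a Data Monitoring Committee is not required for this study", citing among other reasons a known safety profile. On adverse events it says: "Risk management processes are established including reporting pathways for adverse events to the responsible Human Research Ethics Committee".

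**The concern.** Futility means that the planned comparison is unlikely to succeed if the trial goes on. Here that comparison is CRAFT against wait-list. The stated trigger is whether wellbeing improved, assessed once 20 people have finished the programme. Change over time in treated people mixes the programme's effect with natural recovery, regression to the mean and the selection of those who stayed to the end. Completers may also include wait-list participants treated after their six weeks, who no longer have a concurrent control.

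Two errors are possible. A programme that adds nothing can pass because people improve anyway, and a useful one can fail by chance in a small sample. The decision falls at 20 of 260 planned recruits (7.7%), or 20 of the 216 in the sample size calculation (9.3%).

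The adverse-event trigger is a separate matter. It carries no qualifier of severity or relatedness, so read literally any reported event ends the trial.

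**Working it through.** The article gives no error rates for this look, so there is no stated figure to reproduce. From the documents come n = 20, the four instruments and the between-arm hypothesis. The documents give no wellbeing effect size, because the sample size rests on treatment engagement (29% against 15%). The 0.3 SD values and the correlation of 0.6 between scales are therefore assumptions.

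**1. Can the look detect a useless programme?** Assume natural improvement of 0.3 SD of change and no effect of CRAFT. On one scale:

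P(mean change > 0) = Φ(0.3 × √20) = Φ(1.342) = 0.910.

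The trial continues 91% of the time although the between-arm effect is zero. As a range, take natural improvement of 0.2 to 0.3 SD of the outcome and a baseline-to-follow-up correlation r of 0.5 to 0.7, so that the SD of change is √(2(1 − r)) = 1.00 to 0.775 outcome SD:

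- 0.2 SD, r = 0.5: P(stop) = Φ(−0.2 × √20 / 1.00) = Φ(−0.894) = 0.186
- 0.3 SD, r = 0.7: P(stop) = Φ(−0.3 × √20 / 0.775) = Φ(−1.732) = 0.042

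A useless programme is thus stopped in only 4% to 19% of trials.

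**2. How often would an effective programme be stopped?** Assume a total gain of 0.3 SD of change in 20 completers.

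| Meaning given to no improvement | Calculation | P(stop) |
|---|---|---|
| All four scales have mean change ≤ 0, r = 0.6 between scales | four-variate normal, each mean 1.342 | 0.012 |
| One scale has mean change ≤ 0 | Φ(−1.342) | 0.090 |
| One scale is not significant, two-sided 5% | noncentral t, 19 df, noncentrality 1.342, critical value 2.093 | 0.754 |

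If the 0.3 SD natural improvement of step 1 is added to a 0.3 SD effect of CRAFT, the total is 0.6 SD and P(mean change ≤ 0) on one scale is Φ(−0.6 × √20) = Φ(−2.683) = 0.004.

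**3. Would a between-arm reading rescue the look?** Compare 20 completers with 20 controls at a true difference of 0.3 SD of the compared outcome. The standard error is √(2/20) = 0.316 SD, so

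P(wrong sign) = Φ(−0.3 / 0.316) = Φ(−0.949) = 0.171.

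The sign alone would mislead in about one trial in six.

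**4. The adverse-event clause.** With an assumed 1% to 5% chance of a reported event per person, P(at least one among 20) = 1 − 0.99^20 = 0.18 to 1 − 0.95^20 = 0.64. The documents give no event rate, so this shows only how much hangs on the missing qualifier.

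**The case against.** The best defence has five parts.

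- **The text does not say the look is uncontrolled.** It names no comparator but does not exclude one, and the 20 completers may set only the timing. This is correct: uncontrolled is the plain reading, not an express statement. It does not save the rule, because step 3 shows that a between-arm look of this size would also be unreliable.
- **The rule may not be binding.** A decision made collaboratively implies judgement, while the wording about discontinuation is unconditional. The text pulls both ways, so an automatic stop should not be asserted as fact.
- **Thresholds and choice of scale may sit in a fuller document.** That is fair, and their absence is not the point here. The point is that the rule, as stated, addresses a different quantity from the trial's hypothesis.
- **The risk to an effective trial may be small.** A reader might infer that the rule is likely to end a good trial by chance. The documents do not support that. If no improvement means that no scale improves, the risk is about 1%. If people also improve naturally, it is 0.4% on one scale. The 75% needs a significance test that the section never mentions, and a stop triggered by any one failing scale is not what the wording most naturally says.
- **Reporting adverse events to an ethics committee is compatible with considering discontinuation.** This is also right. A reader might see a flat contradiction, but the narrower point is that an unqualified trigger and a routine reporting pathway stand side by side without a stated relation.

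**Conclusion.** The concern holds in this form: the look cannot do what it is labelled to do. It is triggered by completers and names no comparison with wait-list, while the trial tests a between-arm difference by intention to treat. Under 0.3 SD natural improvement and no programme effect, it lets the trial continue 91% of the time (81% to 96% over the range in step 1).

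The chance of wrongly stopping an effective programme is not shown to be high. At a total gain of 0.3 SD it is about 1%, 9% or 75% according to a definition the article leaves open. That spread is itself a reason not to tie discontinuation to this look.

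All these figures rest on assumed effect sizes and correlations. The mismatch between rule and hypothesis does not. The adverse-event trigger is unqualified and needs reconciling with the Ethics and data monitoring section; this review takes no position on which should govern.

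**What to change.** Remove the wellbeing-based stop at 20 completers and keep that look for feasibility and safety review.

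If a futility look is still wanted:

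- make it non-binding;
- base it on the randomised week-6 difference between arms in the primary wellbeing outcome, in all randomised participants, because week 6 is the last scheduled assessment before the wait-list arm is due to start the programme;
- hold it much later, for example when about 108 of 216 (half) have week-6 data;
- state the wellbeing effect it assumes, since the only planned effect in the article is on treatment engagement and a conditional-power rule cannot be computed from it;
- name who sees the comparison by arm. The article keeps the randomisation researcher out of other aspects of implementation, so that role cannot simply be assumed to cover this.

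Reconcile the adverse-event trigger with the reporting pathway and the safety statement under Ethics and data monitoring.

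The cost is a protocol amendment, with ethics and registry updates, in a trial that has already started, and any futility decision comes later. Because sessions run over 6 to 10 weeks, some CRAFT participants will not have finished by week 6, and the assumed effect should allow for that. A non-binding futility look with no efficacy stop spends no alpha.

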## Discussion

This study describes a randomised controlled trial of online delivery of CRAFT, a therapy program for family members concerned about a relative’s substance use. In this program family members whose relative also experiences a mental health condition will be included in the study. There are few substance treatment programs designed for family members even though the family are frequently the ones who provide care and support to people with substance dependence, bearing the brunt of associated health, financial and relationship difficulties [3, 4]. While people with substance problems are not the focus of this study, it does specifically include family members whose relative has both substance dependence and a mental health condition. A similar study [12] found that family members did not know how to talk about substance use with their relative who had a mental illness, even though the substance use was having critically negative effects on their psychiatric treatment. The Family Empowerment Program (CRAFT) offers a structured and tested way to communicate effectively about substance use and its effects, potentially improving mental health treatment for the relative. Any impact in this area will be picked up through the qualitative interviews with participants and will identify areas for future research.

This study will focus on people living in rural areas. Substance treatment programs are limited in rural Australia [8, 9]. The provision of the Family Empowerment Program (CRAFT) online should make family focused substance treatment support accessible and attainable for the first time in many rural areas. The delivery of the program via trained and accredited counsellors assures the fidelity to the CRAFT program and a quality service. These aspects of program delivery will be carefully evaluated through fidelity checklists and follow-up interviews with participants. The outcomes of this trial will have meaningful implications for the future funding and support of family focused substance treatment services that are inclusive of people with mental health conditions.

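### The stopping rule lists reported adverse events as a ground for ending the trial, with no limit on seriousness or relation to CRAFT

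*Protocol article*

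**What the plan says.** The rule is in the Trial duration section of the protocol article. It first sets an early look: "A preliminary analysis will be conducted after 20 participants have completed the program". The stopping grounds follow. The first is a finding of no improvement in well-being, and the sentence continues: "or wellbeing deteriorates or adverse events are reported the trial will be discontinued". The next sentence names who decides: "This decision will be made by the research team collaboratively".

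The Ethics and data monitoring section explains why no data monitoring committee is planned, partly on these grounds: "The population is not particularly vulnerable and the intervention has a known safety profile". On adverse events it adds: "Risk management processes are established including reporting pathways for adverse events to the responsible Human Research Ethics Committee".

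This point concerns the adverse-event ground only. It does not address the futility ground or the deterioration ground.

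**The concern.** The three grounds are joined by *or*, so each stands alone, and all share one firmly worded consequence. The adverse-event ground asks only that events have been reported. As written, an illness or crisis with no connection to CRAFT counts in the same way as serious harm caused by the counselling.

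Unrelated events are plausible here. The Discussion describes families in this position as "bearing the brunt of associated health, financial and relationship difficulties". Under Randomisation and blinding, control participants wait 6 weeks, so an event in that group can occur before any session has been delivered.

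What is at stake is the conduct of a trial planned for 260 people. If the team follows the wording, it could end the trial on evidence that does not bear on safety. If it sensibly continues, it departs from its own published rule, and the rule gives it no criterion to cite in defence.

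**Working it through.** The plan attaches no threshold, error rate or stopping probability to this rule, so there is no figure to reproduce. The check is a reading of the text, followed by an illustration of scale.

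**Step 1. Does anything in the article narrow the ground?**

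- *Trial duration, stopping sentence:* no seriousness, relatedness, number of events or arm is attached.
- *Trial duration, next sentence:* this names the decision-maker and adds no criterion. It does imply some discretion, which sits awkwardly beside a consequence worded as certain.
- *Ethics and data monitoring:* this describes a route for reporting events to the ethics committee. Reporting an event is compatible with the stopping ground and does not restrict it.
- *Elsewhere:* no other section of the article defines or grades adverse events.

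The ground therefore stands as written.

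**Step 2. How often could the literal wording be met if CRAFT caused no harm?**

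Inputs:

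- *n* = 20, the number of completers in Trial duration.
- *p*, the chance that one person has a reported event from any cause. The article does not give this, so it is assumed over a range.
- Independence between people, also assumed.

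Formulae:

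- At least one person with an event: 1 − (1 − p)^20
- At least two people, if the plural is read strictly: 1 − (1 − p)^20 − 20p(1 − p)^19

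For example, at p = 0.01 the first gives 1 − 0.99^20 = 0.182.

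| Assumed p | At least 1 of 20 | At least 2 of 20 |
|---|---|---|
| 0.5% | 9.5% | 0.4% |
| 1% | 18.2% | 1.7% |
| 2% | 33.2% | 6.0% |
| 5% | 64.2% | 26.4% |
| 10% | 87.8% | 60.8% |

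The chance reaches 50% at p = 1 − 0.5^(1/20) = 3.4% for at least one person. For at least two people it does so at about 8.3%, solved numerically.

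**Step 3. Sensitivity to who is counted.** The rule does not say whose events count. If about 40 randomised people across both arms were counted (an assumption), the chance of at least one rises to 33.1% at p = 1%, 55.4% at 2% and 87.1% at 5%.

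The results run from well under 1% to well over one half, depending on the rate, the reading of the plural and the people counted. The article settles none of these.

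**The case against.** The strongest reply is that this is a condensed article. Definitions, grading and causality of adverse events normally sit in the full protocol, which is not shown, and the article says that risk management processes exist. That would answer a complaint that definitions are absent. It does not answer this one, because the article states a trigger and its consequence and states them too broadly. A fuller document that narrowed the trigger would differ from the published rule.

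The second reply is that the following sentence leaves the decision to the research team, so the grounds are matters to be weighed. This largely stands. A reader might infer that any single reported event would automatically end the trial; the two sentences taken together do not support that. What remains is that the stated ground does not help the team to separate relevant events from irrelevant ones.

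The third reply is that the risk may be small, and this also stands. The safety profile is described as known and the population as not particularly vulnerable. The assessment schedule in Table 1 lists no adverse-event instrument, so ordinary background difficulties may never be reported as events. The Discussion's remark about family burden is general and is not a forecast of event rates in this trial.

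Finally, the sentence follows directly on the look at 20 completers, so the ground may be meant for that look only. The wording is too broad on either reading. The article gives no basis for insisting that the rule should run throughout the trial.

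**Conclusion.** The point holds as a minor one. The published rule makes adverse events of any kind a stated ground for discontinuation, and nothing in the article limits it by seriousness or relation to CRAFT. The team's discretion makes an unwarranted stop possible rather than certain, but using that discretion sensibly would mean setting the rule's wording aside.

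The size of the risk is unknown. The percentages above rest wholly on assumed rates and on independence. A reader might take them as the probability that the trial stops, but they show only how often the literal wording would be met. A reader might also infer that the treatment comparison is compromised. Nothing here biases the effect estimate or the randomisation, and any error is towards caution for participants. The exposure is an unnecessary stop, or a decision that is hard to defend against the published text.

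**What to change.** Replace the adverse-event ground with: *serious adverse events judged at least possibly related to the intervention, or a pattern of intervention-related harm, are found on review by arm*.

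For this ground only, replace automatic discontinuation with a documented continue-or-stop decision by the research team, reported to the ethics committee through the existing pathway. The decision should stay with the team, because the article describes the ethics-committee route as a reporting pathway only.

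The cost is a wording change, notification of the ethics committee and a brief relatedness judgement for each reported event. The downside is a less automatic stop, although serious related harm would still lead to a recorded decision. No extra participants are needed. This is a cheap improvement.
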